### Statistics

#### Sample size

Among women who have adjuvant therapy plus axillary treatment, 2% have axillary recurrence within 5 years.^11^ A total of 1700 women is required for analysis (850 in each group) in order to detect a non-inferiority margin of two percentage points for the risk difference using the Miettinen-Nurminen score interval,^12^ with 80% power and 2.5% one-sided alpha. Allowing for up to 10% non-compliance with treatment allocation and non-collection of primary outcome data, the target sample size to be randomised is 1900.

The magnitude of the non-inferiority margin was determined following consultation with relevant breast cancer consumer groups, lay people, breast surgeons and oncologists. There was consensus across all groups that an absolute increase in axillary recurrence of up to 2% is an acceptable trade-off for the increase in arm morbidity associated with axillary treatment.

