#### Statistical analysis

Analysis will be at the end of the 5-year follow-up of the last recruited participant. A detailed statistical analysis plan will be developed by the trial statisticians in consultation with the Trial Management Group, and agreed with the Trial Steering Committee before database lock and unblinding of data.

Descriptive statistics of demographic and clinical measures will be used to assess balance between the randomised arms at baseline. Continuous variables will be summarised in terms of the mean, SD, median, lower and upper quartiles, minimum, maximum and number of observations. Categorical variables will be summarised in terms of frequency counts and percentages.

The primary approach for between-group comparative analyses of primary and secondary endpoints will be per protocol, and we will present point estimates and 95% CIs. Sensitivity analysis where participants are analysed as randomised, regardless of compliance with allocation, will also be conducted for the primary outcome.

The primary analysis will assess whether adjuvant therapy alone is non-inferior to adjuvant therapy plus axillary treatment based on the primary endpoint of axillary recurrence within 5 years. The risk difference will be estimated using a mixed effects generalised linear model for binary outcome, with treatment arm and minimisation variables as fixed effects and recruitment site as a random effect. Non-inferiority of adjuvant therapy alone compared with adjuvant therapy plus axillary treatment will be accepted if the upper boundary of the Miettinen-Nurminen two-sided 95% confidence limit for estimated difference in axillary recurrence is no greater than 2%.

We will conduct subgroup analyses of axillary recurrence and arm morbidity by fitting appropriate interaction terms in the regression models, according to the following variables measured at baseline: number of sentinel node macrometastases; age; type of breast surgery; ER status; tumour grade; sentinel node assessment technique; extranodal invasion. We will present subgroup-specific effects and 95% CIs, as well as interactions, 95% CIs and p values. Due to the limited power available to detect all except large interactions, these subgroup analyses will be regarded as exploratory and interpreted with due caution.

Analyses for surgical complications following treatment of ANC will be of a descriptive nature.

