Cost-effectiveness analysis based on the incremental cost per reduction in axillary recurrence. Mean costs for each randomised arm will be calculated as will mean axillary recurrence and will be presented as point estimates of mean incremental costs and effects (reduced axillary recurrences) and the incremental cost per reduction in axillary recurrence at 5 years post randomisation.Cost-utility analysis based on the incremental cost per QALY gained. QALYs will be based on the area under the curve approach^15^ using responses to the EQ-5D-5L completed at scheduled time points; baseline, 3, 6, 12, 24, and 36 months post-randomisation. The total average QALYs accruing in the intervention and standard care groups will be analysed for significant differences, following allowances for mortality (if occurring). Both mean cost and QALYs will be presented for each randomised group and incremental mean costs and QALY calculated along with the incremental cost per QALY gained at 3 years post randomisation.

Both deterministic and stochastic sensitivity analyses will be used to address any uncertainty in our estimation of costs, effects and cost-effectiveness. Any uncertainty in the results, based on the stochastic sensitivity analyses, will be illustrated using cost-effectiveness planes and cost-effectiveness acceptability curves. Costs and effects will be discounted at UK recommended rates^16^ as they are being estimated beyond a 1-year time horizon.

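### The cost-utility analysis describes incremental QALYs as a difference in arm means and names no adjustment for the baseline EQ-5D-5L that the trial collects

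*Protocol article*

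**What the plan says.** All of this is in the protocol article.

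- **Economic analysis, construction of QALYs.** "QALYs will be based on the area under the curve approach", with EQ-5D-5L "completed at scheduled time points; baseline, 3, 6, 12, 24, and 36 months post-randomisation".
- **Economic analysis, comparison.** "The total average QALYs accruing in the intervention and standard care groups will be analysed for significant differences, following allowances for mortality (if occurring"). Mortality is the only allowance mentioned.
- **Economic analysis, increment.** Mean cost and mean QALYs are shown by randomised arm, and "incremental mean costs and QALY calculated along with the incremental cost per QALY gained at 3 years post randomisation".
- **Statistical analysis.** For axillary recurrence a model is specified, "with treatment arm and minimisation variables as fixed effects and recruitment site as a random effect". Per protocol is the primary approach for primary and secondary endpoints; an as-randomised sensitivity analysis is stated for the primary outcome only.
- **Table 1.** EQ-5D-5L and incremental cost per QALY are listed among the secondary outcomes.
- **Randomisation.** Allocation is stratified by site and minimised on age, type of breast surgery, ER status, number of positive nodes and OSNA use. EQ-5D-5L is not among these factors.
- **Deferral.** "A detailed statistical analysis plan will be developed by the trial statisticians in consultation with the Trial Management Group". That plan is not shown.

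**The concern.** A woman's utility at baseline predicts her utility at later visits. If one arm starts slightly higher by chance, its area under the curve will on average be higher too, whatever the treatment does. A plain difference in arm means counts that head start as part of the incremental QALY. Minimisation does not act on EQ-5D-5L, so nothing in the design limits the imbalance beyond randomisation itself.

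The incremental QALY is the denominator of the cost-utility ratio. The section itself expects any quality-of-life difference between the arms to have gone by 3 years, so the true increment may be small. A chance shift in a small denominator can alter the ratio noticeably, and variance that could have been removed widens the acceptability curve.

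The section also goes further than leaving the method open. It sets out the calculation in steps, and baseline adjustment is not one of them, whereas the primary outcome has its covariates listed.

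**Working it through.** **The plan's own figures.** The document states no SD, correlation or target difference for QALYs, so there is no QALY figure to reproduce. The 850 per arm used below is the analysed number for the primary outcome (Sample size section). That number does reproduce: with 2% recurrence in both arms and a 2-point margin, the Miettinen-Nurminen test at 850 per arm has 80.6% power by simulation, and 1700 / 0.9 = 1889, close to 1900. It is not a count of women with complete EQ-5D-5L.

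**Inputs from the document.** Visits at 0, 0.25, 0.5, 1, 2 and 3 years.

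**Assumptions (not in the document).** Utility SD s = 0.20 at every visit; the same correlation ρ between any two visits, 0.4 to 0.7; 850 per arm; no deaths, missing data or discounting.

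**Step 1: weight of each visit.** The trapezoid rule gives 0.125, 0.25, 0.375, 0.75, 1.0 and 0.5 years, which sum to 3.0. Baseline's direct share is 0.125 of 3.0. The other visits carry 2.875.

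**Step 2: slope of the 3-year QALY on baseline utility.** Slope = 0.125 + 2.875ρ.

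**Step 3: variance of the 3-year QALY.** The squared weights sum to 2.03125, so variance / s² = 9ρ + 2.03125(1 − ρ).

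**Step 4: share of variance explained by baseline.** r² = slope² / (variance / s²). This is the proportional cut in variance from adjustment. It depends neither on s nor on the sample size.

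**Step 5: chance imbalance.** The standard error of the baseline difference is 0.20 × √(2/850) = 0.0097. Its effect on the QALY difference is slope × 0.0097. The unadjusted standard error is 0.0097 × √(variance / s²), and the adjusted one is that times √(1 − r²).

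| ρ | Slope | Variance / s² | r² | QALY shift per one-SE imbalance | SE unadjusted | SE adjusted |
|---|---|---|---|---|---|---|
| 0.4 | 1.275 | 4.819 | 0.34 | 0.012 | 0.0213 | 0.0173 |
| 0.5 | 1.563 | 5.516 | 0.44 | 0.015 | 0.0228 | 0.0170 |
| 0.6 | 1.850 | 6.213 | 0.55 | 0.018 | 0.0242 | 0.0162 |
| 0.7 | 2.138 | 6.909 | 0.66 | 0.021 | 0.0255 | 0.0148 |

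The relevant correlation is that of baseline with the whole area under the curve. Squaring the visit-to-visit ρ instead would give 16% to 49%, which understates the gain, because averaging over visits raises the correlation.

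**Sensitivity to the SD.** The shift scales with s. At s = 0.15 and ρ = 0.4 it is 0.00728 × 1.275 = 0.009; at s = 0.25 and ρ = 0.7 it is 0.01213 × 2.1375 = 0.026. At the 95% limit of chance imbalance (1.96 standard errors) with s = 0.20, it is about 0.024 to 0.041.

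**The case against.** **The analysis plan may already adjust.** A reader might infer from the Economic analysis section that the trial will use a raw, unadjusted difference. The text does not say so. Analysing average QALYs for differences names no model, and an adjusted regression also yields incremental mean QALYs. A condensed article may leave covariates to the analysis plan. This stands: the point can only be that adjustment is not named, and not that it will be omitted. It does not remove the point, because the steps as described lead to a difference in arm means, and the plan still to be written is the natural place to improve on them.

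**Randomisation already protects the comparison.** A reader might infer a biased result. In an as-randomised comparison the unadjusted difference is unbiased in expectation, chance imbalance is ordinary sampling error, and a valid unadjusted interval already includes it. The planned stochastic analyses and acceptability curves would display that uncertainty. This also stands. What remains is lost precision and imbalance in the one sample obtained.

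The protection is weaker if per protocol governs the QALY comparison, since exclusions after randomisation can be related to baseline health. The document does not settle this. The Statistical analysis section and Table 1 together point to per protocol, while the Economic analysis section speaks of randomised groups.

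**Baseline counts for little in the curve.** Its direct weight is only 0.125 of 3.0 years, so it would be wrong to say that the whole imbalance persists for three years. The carry-over is partial and depends on the correlation, which the slope in the table takes into account.

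**No benchmark for a meaningful QALY difference.** The document gives none. Even a constant difference of 0.02 to 0.03 over 3 years, which would mean 0.06 to 0.09 QALY undiscounted, sits badly with the section's own expectation that differences fade. So the shift can be given in QALYs, but the document does not support a claim that it would reverse the conclusion.

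**Conclusion.** The point holds as a minor one. As described, the incremental QALY is a difference in arm means with no baseline adjustment named, although baseline EQ-5D-5L is collected and is not balanced by design. At SD 0.20 and 850 per arm, one standard error of baseline imbalance moves the 3-year QALY difference by about 0.012 to 0.021, and adjustment would cut its variance by about 34% to 66% (standard error by about 19% to 42%) for inter-visit correlations of 0.4 to 0.7.

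These sizes rest on assumed SD and correlations, on equal correlation between visits, and on no deaths, missing data or discounting. Fewer women with complete EQ-5D-5L would make the imbalance larger; a correlation that decays over time would make the carry-over and the gain smaller than shown for a given early-visit correlation. The primary non-inferiority conclusion on axillary recurrence is not affected.

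**What to change.** In the analysis plan or health economics plan, before unblinding:

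1. Estimate the incremental QALY by regressing individual 3-year QALYs on arm, baseline EQ-5D-5L index and the minimisation factors.
2. Keep the correlation between costs and QALYs, for example by seemingly unrelated regression or by bootstrapping cost-QALY pairs with the adjustment repeated in each resample.
3. Use the adjusted increment in the cost per QALY, the cost-effectiveness plane and the acceptability curve. Arm means can still be shown descriptively.
4. State whether the QALY comparison is as randomised or per protocol.

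The cost is a few lines of analysis wording. Baseline EQ-5D-5L is already collected, and neither the sample size nor the visit schedule changes.

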### Radiotherapy quality assurance

The UK Radiotherapy Trials Quality Assurance (RTTQA) Group will be responsible for implementing and coordinating the radiotherapy quality assurance (RT QA) programme through a named contact for the trial. The programme includes pre-trial and on-trial activities and is outlined below:

Pretrial QA—prior to site activation

Facility questionnaire—Details of treatment technique, immobilisation, verification and dosimetry will be recorded.Dummy run—All centres must submit a test participant case to the RTTQA group, for review, demonstrating planned RT treatment to the breast/chest wall, axilla and supraclavicular fossa. The outlining, planning and treatment of this participant case should reflect how the centre intends to plan and treat all participants recruited to POSNOC.

On-trial QA—Ongoing QA during trial recruitment

Retrospective individual case reviews —All centres must export RT plan data to the RTTQA Group for their first ten participants. Data will include participant history, CT data, structure set, plan and dose files. The retrospective review process should include at least three plans with RT to the nodal region.Ongoing data collection—RT data related to the RT QA programme will be collected and stored by the RTTQA Group for all participants, regardless of study allocation. A random sample of plans will be reviewed from each site during the trial recruitment period.

The sites will be required to adhere to the POSNOC RT planning and delivery guidelines when treating participants in the study. The RTTQA Group will promote and monitor compliance to the guidelines for the duration of trial recruitment by systematically reviewing a sample of RT plans submitted by centres. RT guideline deviations, non-compliance or areas of concern will be recorded and if required, discussed with the TMG and individual centres.

### Patient and public involvement

As part of the development of the project and protocol, women from the Derby Breast Cancer Support Group, Bosom Buddies (Guildford Breast Cancer Support Group) and Independent Cancer Patients’ Voice (ICPV) have commented at all stages on the design and acceptability of the study. The Breast Cancer Care and Lymphoedema Support Network have had the opportunity to contribute to this protocol.

ICPV is an independent patient advocate group (http://independentcancerpatientsvoice.org.uk/). Two members of ICPV will provide a patient perspective throughout the duration of the study.

### Ethics and dissemination

The study has been approved by the National Research Ethics Service Committee East Midlands—Nottingham 2 (REC reference: 13/EM/0459).

The dissemination of the study results will be via a study report and research papers for publication in peer-reviewed journals, and presentation at relevant conferences. Reporting will be in compliance with Consolidated Standards of Reporting Trials recommendations. Publication of the results will be based on outcomes at 5 years following the last recruited participant.

A summary of the results will be made available to participants through a newsletter (unless they state they do not wish to receive this), and will also be publicised through ICPV, Cancer Research UK, Breast Cancer Now and Lymphoedema Support Network.
